## Abstract

**Background::**

In recent years, the incidence of ulcerative colitis (UC) is on the rise, and most of them are young adults. As the peak of the disease overlaps with the childbearing age, it has a great impact on the fertility of female patients. We, therefore, conduct a randomized and controlled trial to evaluate the efficacy and safety of mesalazine enteric-coated tablets combined with Kangfuxin Liquid (KFX) enema for the child-bearing period female with active UC.

**Methods::**

In this randomized controlled study, a total of 236 eligible patients will be assigned to the experimental group (n = 118) or the control group (n = 118) in a 1:1 ratio. The control group will be taken mesalazine enteric-coated tablets combined with placebo enema and the experimental group will be taken mesalazine enteric-coated tablets combined with KFX enema. Participants will receive 8 weeks of intervention treatment and 3 months of maintenance treatment before pregnancy. The primary assessment is the Mayo score. Secondary outcomes include mucosal healing, faecal calprotectin (FC), Inflammatory Bowel Disease Quality (IBDQ), and pregnancy outcome.

**Discussion::**

This study will provide evidence regarding the efficacy and safety of KFX enema used before pregnancy on halting active UC, reducing the relapse rate during pregnancy, improving pregnancy outcome, and the quality of life.

**Trial registration::**

Chinese Clinical Trials Register identifier, ChiCTR2000039161, registered on October 20, 2020.

## Introduction

1

Ulcerative colitis (UC) is one of the two inflammatory bowel diseases (IBD) characterized by bloody diarrhea, abdominal pain, and mucus stools. According to a systematic review,^[1]^ Europe has the highest annual incidence of UC—24.3 per 100,000 people. Although the number in Asia and the Middle East is only 6.3 per 100,000 people, in these countries such as Japan and China, the incidence of UC has been increasing remarkably.^[2,3]^ Not only the intestinal symptoms of UC itself but also its impact on all aspects of the daily life of patients, especially females, have received considerable critical attention. Of particular concern is that UC occurs most frequently in the young female with the highest incidence peak in the second or third decades of life^[4]^ which is the essential prime reproductive age for women.

In recent years, there has been an increasing amount of study on the impact of the female with UC on pregnancy and neonatal. Many pieces of evidence show that pregnant women with UC have a higher incidence rate of abnormal pregnancy and delivery, such as the delivery of premature, low birth weight infants, and venous thromboembolism (VTE) risk in both pregnancy and the postpartum period than those without UC, and there are significant differences in active UC.^[5–7]^ Furthermore, female with UC increased the risk of infant birth defects overall. In a retrospective cohort study^[8]^ of 7798 cases of UC in Quebec, Canada between 1989 and 2016, UC was associated with 1.53 times the risk of central nervous system defects. Another study^[9]^ concluded that neonatal are at an elevated risk of limb and urinary defects. The problem about the damages of UC medication to their unborn children or heredity increases their fertility concerns.^[10]^ Guideline^[10]^ recommends that women plan to get pregnant when in remission. However, it cannot be ignored that an increased risk for UC relapse during pregnancy^[11]^ Similarly, a meta-analysis^[12]^ by Abhyankar et al has demonstrated that the recurrence rate and severity of UC influenced by disease activity at the time of conception. In addition, several lines of evidence suggest that UC has an interactive relationship with Anxiety and Depression (A&D). Individuals with UC are at increased risk of A&D. Meanwhile, UC with comorbid A&D are more challenging to manage. The selective protective effect of antidepressant treatment on UC confirms that it has a two-way relationship with A&D^[13,14]^ A prospective cross-sectional study^[15]^ in the United States or Denmark suggest that activity UC significantly correlated with sexual dysfunction. Besides, it exacerbates dysmenorrhea and gastrointestinal symptoms during menstruation.^[16]^ Overall, for females with UC, there are unique challenges in a different decade of life, spanning from menstruation, sexual health, mental health to fertility, and pregnancy. Consequently, It is essential for the patients to have optimal management of UC prior to and during pregnancy to achieve favorable maternal and neonatal outcomes, and preferable quality of life.^[17]^

Mesalazine, a first-line treatment for mild to moderate UC, is recommended to continue to be used during pregnancy to reduce the significant increase of relapse rate.^[17]^ It is classified as Class B by the Food and drug administration which is safe and tolerable.^[18]^ However, there are still 23.6% to 36.5% of patients who have undergone standard treatment with mesalazine with unsatisfactory mucosal healing (endoscopy score ≥ 2) and even worsening of the symptom during the 12 months follow-up.^[19,20]^

As integrative therapy or alternative medicine, traditional Chinese medicine (TCM) is safe and economical in improving symptoms. In recent decades, magnanimous evidence from clinicians suggests that TCM has some beneficial effect on UC.^[21–23]^ Kangfuxin Liquid (KFX) is an extract of Periplaneta americana dried worms, which has been approved by the National Medical Products Administration (Z51021834). Periplaneta americana is an insect of the cockroach family, recorded in Shen Nong Ben Cao Jing more than 2000 years ago in China, included many active substances such as polyols and peptide which presented the bioactive functions of anti-inflammation and promoting mucosal barriers repair.^[24]^ Periplaneta americana has been diffusely applied in China against various diseases. Modern research indicates that the Periplaneta americana prevents inflammatory responses to protects against renal and hepatic fibrosis, accelerates mucosal healing by increasing the expression of EGF and VEGF in granulation tissueim.^[25–27]^ Over the past decade, it has been emphasized the effect of Periplaneta americana on the gastrointestinal ulcer. It is now well established that Periplaneta americana is effective and safe for gastrointestinal ulcer patients from a variety of studies including clinical trials, animal experiments, and system analysis.^[28–32]^ However, KFX treatment before pregnancy has not been evaluated in detail in terms of improving or maintaining the progression of UC from before, during pregnancy to childbirth. We designed an RCT to evaluate the effects of mesalazine combined with KFX enema before pregnancy on halting active UC, reducing the relapse rate during pregnancy, improving pregnancy outcome, and the quality of life.

## Methods and analysis

2

### Study design

2.1

This study is designed as a randomized, controlled, double-blind trial. With mesalazine enteric-coated tablets as the control, to explore the efficacy of mesalazine combined with KFX enema in the treatment of active UC in women with fertility requirements and to improve pregnancy outcome and quality of life, reduce the recurrence rate. Prospective participants will be asked to talk face to face with the researcher for a baseline screening visit after diagnosis. After the 8 weeks of treatment, they will be followed for another 3 months of maintenance therapy. This study will start in October 2020 and continue until April 2022. The study schedule is detailed in Table 1. The flowchart of the trial is shown in Figure 1.

**Table 1 T1:** Data collection points.

	Screening	Randomization	treatment	Follow-up (maintenance therapy)	Follow-up (pregnancy until delivery)		
Visits	①	②	③	④	⑤	⑥	⑦
Time point	4 weeks before treatment	Day 0	Weeks 1–8	Weeks 9–20	Months 0–3	Months 4–6	Months 7 to delivery
Age	X						
Duration of disease	X						
Disease history	X						
Comorbidity	X						
Clinical examination	X						
control group							
experimental group							
Mayo score	X		X	X			
Mucosal healing	X		X	X			
IBDQ	X		X	X	X	X	X
Faecal calprotectin	X		X	X	X	X	X
pregnancy outcome					X	X	X
Adverse events			X	X	X	X	X
Causes of dropout			X	X	X	X	X
Data analysis							X

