### Sample size

2.6

The sample size was determined by the primary study results. According to previous reports, the effective rate of the experimental group based on the Mayo, score ranges from 57.5% to 76.47%,^[35,36]^ and the average rate is about 66.99%. The effective rate of the control group ranges from 41.25% to 55.65%,^[22,37]^ and the average rate is about 48.45%. We will use the following formula to estimate sample size:$${\text{n}}_{\text{c}}=\frac{[\pi_{t}(1-\pi_{t})/k+\pi_{c}(1-\pi_{c})]{\left(u_{1-\partial /2}+u_{1-\beta }\right)}^{2}}{{\left(\pi_{t}-\pi_{c}\right)}^{2}}$$

With a 5% significance level (α = 0.05), 80% Power (β = 0.2), and 10% dropout rate, at least 118 patients should be enrolled in each group and 236 total participants will be recruited.

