## Interventions

3

In the experimental group, mesalazine enteric-coated tablets (supplied by LOSAN Pharma GmbH 0.5 g/tablet) will be taken orally 1.0 g per time and 3 times a day for 8 weeks continuously. At the same time, the KFX (supplied by Sichuan Good doctor Panxi Pharmaceuticals) will be given retention enema treatment 100 mL per time, 1 time a day. KFX need to be heated to 37°C and poured into a one-time enema bag. The enema tube will be inserted into the anus for about 10 cm. The control group enteric-coated mesalazine tablets will be taken orally 1.0 g per time and 3 times a day for 8 weeks. The enema method of placebo is the same as that of the treatment group. During the treatment period, patients in both groups avoid irritant and crude fiber food and supplemented with an adequate amount of folic acid (2 mg/d). Eight weeks later, according to the guidelines,^[17]^ UC patients in remission (Mayo score ≤2 and normal intestinal mucosa or no active inflammatory) will continue to be treated with maintenance therapy Maintenance therapy is based on the treatment mentioned above, but the dose is reduced (mesalazine 0.5 g/time, 3 times/day, KFX/placebo enema 50 mL) for 3 months. Subsequently, the patient in stable condition will be given active pregnancy guidance. Both groups of patients change to oral mesalazine (0.5 g/time, 3 times/day) from pregnancy to delivery. Due to a lack of research on the safety of KFC being used during pregnancy, KFX will be discontinued once patients in remission enter the active pregnancy preparations stage. All drugs should be the same lot number. In the course of the study, it is forbidden to add other drugs or interventions that may interfere with the trial. Cases in which symptoms have not alleviated or even aggravated, the participants voluntarily withdrew, and no medication or any follow-up records due to poor compliance will be regarded as excluded cases, and participants will be required to complete the assessments as much as possible.

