### Trial status

5.1

The recruitment of patients started on October 30, 2020, and it is expected that by January 30, 2021, the required sample size will be reached. This protocol was submitted before completion of recruitment.

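### The April 2022 study end conflicts with follow-up to delivery: the last entrant has about 7 weeks to conceive and still reach a term delivery on study, so absolute pregnancy and live-birth rates are truncated

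*Protocol article*

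**What the plan says.** Section 2.1 (Study design) fixes the calendar: "This study will start in October 2020 and continue until April 2022". Section 5.1 (Trial status) fixes entry: "The recruitment of patients started on October 30, 2020, and it is expected that by January 30, 2021, the required sample size will be reached".

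Pregnancy attempts come late in each woman's course. Section 2.1 states "After the 8 weeks of treatment, they will be followed for another 3 months of maintenance therapy", and Table 1 places treatment and maintenance in weeks 1 to 20, with a screening visit "4 weeks before treatment". Section 3 (Interventions) then says "Subsequently, the patient in stable condition will be given active pregnancy guidance".

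Table 1 carries three pregnancy visits, the last labelled "Months 7 to delivery", and puts data analysis at that visit. Section 4.2 lists pregnancy rate, abnormal pregnancy rate and live birth rate as secondary outcomes. Abnormal pregnancy there includes events known only at or near delivery (prematurity, low birth weight, congenital defect) and events that can appear sooner (abortion, threatened abortion, venous thromboembolism). Section 4.5 analyses categorical data by chi-square or Fisher test under intention to treat, with multiple imputation for missing values.

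**The concern.** Follow-up to delivery is a stated design feature, and so is the end date. If a woman cannot finish treatment, conceive and carry to term before April 2022, the two statements cannot both hold for her.

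Three things follow. A woman who conceives after her last feasible date is still pregnant at the cut-off, so her birth is not counted. Women who enter early have longer to conceive than women who enter late, so a single percentage pools unequal exposure. Pregnancies that end early are complete by the cut-off more often than term pregnancies, so the completed ones are not representative.

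Improving pregnancy outcome is among the stated aims (Abstract, sections 1, 2.1 and 5), and it is what sets this trial apart from a general ulcerative colitis trial. Readers may also take absolute live-birth and abnormal-pregnancy rates as safety information.

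**Working it through.** The article gives no figure for the time available to conceive, so there is none to reproduce on this point. Its one computed figure, 118 per group, rests on the Mayo effective rates of 66.99% and 48.45%. The stated formula gives 107.5, and 107.5 × 1.1 = 118.3. That figure is not touched by what follows.

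**Inputs from the article**
- First and last entry: 30 October 2020 and 30 January 2021 (section 5.1).
- Study end: April 2022, read as 1 April at the earliest and 30 April at the latest (section 2.1).
- Time before pregnancy attempts: 20 weeks = 140 days (Table 1), or 8 weeks plus 3 calendar months = 56 + 92 = 148 days.
- Screening lead: 4 weeks = 28 days, added if the entry date is a screening date (Table 1).

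**Input assumed**
- Conception to term delivery: 38 weeks = 266 days, with a range of 35 to 40 weeks.

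**Formula**

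Window = (study end − gestation) − (entry date + any screening lead + time before pregnancy attempts).

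**Last entrant, most favourable dates**
- 30 January 2021 + 140 days = 19 June 2021.
- 30 April 2022 − 266 days = 7 August 2021.
- Window = 49 days = 7.0 weeks.

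**First entrant, same reading**
- 30 October 2020 + 140 days = 19 March 2021.
- Window to 7 August 2021 = 141 days = 20.1 weeks.

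**Other readings of the dates, in weeks, at 38 weeks of gestation**

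| Study end | Entry date is | Last entrant, 20 weeks | Last entrant, 8 weeks + 3 months | First entrant, 20 weeks |
|---|---|---|---|---|
| 30 April | day 0 | 7.0 | 5.9 | 20.1 |
| 1 April | day 0 | 2.9 | 1.7 | 16.0 |
| 30 April | screening | 3.0 | 1.9 | 16.1 |
| 1 April | screening | −1.1 | −2.3 | 12.0 |

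A negative value means that no term delivery on study is possible.

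**Sensitivity to gestation (last entrant, day 0, 30 April)**

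She has 45.0 weeks from the end of maintenance to the study end. The window is 45 − 35 = 10.0 weeks, 45 − 38 = 7.0 weeks, or 45 − 40 = 5.0 weeks. The same numbers show the selection: a delivery at 35 weeks is observed for conceptions up to 3 weeks later than a delivery at 38 weeks.

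**What the windows could mean for conception (illustration only)**

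Assume a constant probability f of conceiving per 4 weeks, with f from 15% to 25%. The share conceiving within w weeks is 1 − (1 − f)^(w/4).
- 7 weeks: 1 − 0.85^1.75 = 25%, to 1 − 0.75^1.75 = 40%.
- 20 weeks: 1 − 0.85^5 = 56%, to 1 − 0.75^5 = 76%.

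The date conflict does not depend on these values of f.

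**Direction of distortion**
- Live-birth rate: down, if ongoing pregnancies count as no live birth.
- Abnormal-pregnancy rate among completed pregnancies: up, because losses and preterm births complete sooner.
- Abnormal-pregnancy rate among all pregnancies or all randomised women: down, because late events in ongoing pregnancies are not yet seen.

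**The case against.** Five points weigh against a harsher reading, and most of them stand.

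- **Both arms share the cut-off.** A reader might infer that the treatment comparison is biased. Allocation is 1:1 and the same calendar applies to everyone, so truncation alone does not favour an arm. Bias needs the arms to differ in time to conception, in the share going on to pregnancy, or in gestation length. The second is conceivable, since only women in remission proceed and the trial hopes to raise remission, but the article does not establish it.
- **The direction for abnormal pregnancy is open.** A reader might infer that this rate is inflated. That holds only among completed pregnancies, a denominator that section 4.2 does not state. Threatened abortion and thromboembolism also need not wait for delivery.
- **Seven weeks describes the last entrant and depends on an assumed gestation.** Other women fall between her and the first entrant. This stands, which is why the range is shown.
- **Analysis detail may sit elsewhere.** Denominators, censoring and the handling of ongoing pregnancies can be left to a full protocol or analysis plan, and section 4.5 does name multiple imputation. Their absence from the article is not the point. The point is the conflict between two stated design features, which an analysis plan cannot remove without changing one of them or redefining the outcomes.
- **The outcomes are secondary.** The Mayo score at week 8 and after maintenance is complete well before April 2022, even for the last entrant.

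**Conclusion.** The point holds as a conflict within the article and should be fixed. At the stated dates, follow-up to delivery is not achievable for every woman who conceives. The last entrant has about 7 weeks to conceive and still deliver at term on study, assuming 38 weeks of gestation, a 30 April 2022 end and treatment starting on 30 January 2021. Less favourable readings of the dates leave about 3 weeks or none. The first entrant has about 16 to 20 weeks (12 if the end is 1 April and her entry date is also a screening date). The close of recruitment is only an expectation; each week of slippage takes a further week from the last entrant.

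The sure consequences are truncated absolute pregnancy and live-birth rates, unequal exposure within each arm, and a between-arm comparison with fewer events and less precision. A reader might go further and conclude that the trial cannot address pregnancy at all. The documents do not support that: early entrants have a usable window, and the comparison remains randomised.

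**What to change.** **Preferred.** Set one common observation window for conception, counted from week 20, for every woman. Amend the end date of pregnancy follow-up so that the last woman's window plus a full pregnancy fits. With her week 20 on 19 June 2021 and 38 weeks of gestation, a 20-week window needs follow-up to 30 July 2022 (13 weeks past 30 April), and a 52-week window needs 11 March 2023 (45 weeks past). Allowing 40 weeks of gestation adds 2 weeks to either. The cost is an amended end date and later reporting of the secondary pregnancy outcomes; the Mayo results are not delayed.

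**If April 2022 is kept.** State the exact closing date, then:
- analyse time from randomisation to conception in all randomised women, censored at the cut-off;
- report ongoing pregnancies as a separate category, not as failures;
- present delivery-based rates among conceptions early enough to reach term as descriptive only, because that subset is defined after randomisation.

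This needs only wording, but it gives up a randomised comparison of delivery outcomes in that subset and does not recover the lost events. Either change should be made before the cut-off, since deliveries not followed at the time may not be recoverable afterwards.

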**Figure 1 F1:**
[figure not shown]
Trial flow chart.

### Ethic approval

2.2

The research protocol is conducted in accordance with the principles of the Declaration of Helsinki^[33]^ and has been approved by the Sichuan Regional Ethics Review Committee on Traditional Chinese Medicine (approval no. 2019KL-072). Also, this trial has been registered in the Chinese Clinical Trial Registry (Registration No. ChiCTR2000039161).

### Participants

2.3

A total of 236 women in the child-bearing period with UC will be recruited after signed the informed consent. They will be invited to the Department of gynecology, Teaching Hospital of Chengdu University of Traditional Chinese Medicine. The printed recruitment posters will be post in the hospital to recruit participants. All participants should meet the diagnostic criteria according to the Chinese consensus on the diagnosis and treatment of IBD.^[34]^ Eligible participants will be implemented randomly with a 1:1 allocation ratio in the control group with (n = 118) or the experimental group (n = 118).

### Inclusion criteria

2.4

Patients who meet all of the following conditions will be considered for enrollment. The inclusion criteria are as follows:

1.Females, aged between 20 and 45 years;2.Patients who meet the criteria of active UC refer to Chinese consensus on diagnosis and treatment;3.Patients preparing for pregnancy;4.Patients who willing to participate in the study, sign an informed consent and can be followed up

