### Randomization and blinding

2.7

Participants will be randomly allocated according to a random list of numbers generated with SPSS21.0 software. Opaque envelopes containing an allocation sequence number will be used by an independent staff who needs to prepare the assignments and conceal the allocation sequence. Blinding will be strictly maintained to intervention staffs, participants, the statistician, and staff who obtained outcome measurement. They will not know the corresponding relations between numbers and different groups. By using an identical liquid placebo in color, consistency, and smell to the KFX, blinding will be ensured.

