### Statistical analysis

4.5

The statistician performs Statistical analyses of data by using SPSS21.0 software (International Business Machines Corp., Armonk, NY). Intention-to-treat principle approach for efficacy and safety analysis will be used. As dealing with the missing values, multiple imputations method will be applied. Continuous variables with normal distribution, expressed as Mean ± Standard Deviation, will be analyzed by *t* test. In contrast, nonparametric tests will be adopted when variables are kept in the abnormal distribution. Categorical data presented by frequency and percentage will be analyzed by the chi-square test or Fisher exact test. All the tests will be conducted two-sided, and a *P*-value < .05 will be considered as the significant level.

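### Pregnancy and live-birth rates are compared without adjusting for age, although eligibility runs from 20 to 45 and age is already recorded: a valid test, but a free gain in precision is left unused

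*Protocol article*

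**What the plan says.** - **Who is enrolled.** Inclusion criteria (2.4): "Females, aged between 20 and 45 years", and preparing for pregnancy.
- **What is collected.** Table 1 in Study design (2.1), titled "Data collection points", marks age at the screening visit.
- **How women are allocated.** Randomization and blinding (2.7): "Participants will be randomly allocated according to a random list of numbers generated with SPSS21.0 software". No stratification factor is named.
- **Which outcomes are affected.** Secondary outcomes (4.2) lists pregnancy rate, abnormal pregnancy rate and live birth rate, all as percentages.
- **How they are tested.** Statistical analysis (4.5): "Categorical data presented by frequency and percentage will be analyzed by the chi-square test or Fisher exact test". No covariate or adjusted model is named. Tests are two-sided at 0.05 and follow intention to treat.
- **What the trial is sized on.** Sample size (2.6) uses the Mayo effective rate, not pregnancy.

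**The concern.** Age can be expected to affect conception, and the entry range is 25 years wide. As described, nothing in the design balances age and nothing in the analysis uses it. Two things are then at stake for the pregnancy and live-birth comparisons. First, variation in outcome that age could explain stays in the error term, so the comparison is less precise than the data allow. Second, if the arms happen to differ in age, the unadjusted difference carries that imbalance, and a reader of the baseline table will ask how much of the result is due to age. An adjusted analysis added only after such an imbalance had been seen would be open to the charge of being chosen for its result. This is a stated method that can be improved, not a detail that the article has left out.

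**Working it through.** **1. The plan's own figure.** The inputs are control "the average rate is about 48.45" per cent, experimental "the average rate is about 66.99" per cent, two-sided 0.05, 80% power, k = 1.

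n = [0.6699 × 0.3301 + 0.4845 × 0.5155] × (1.960 + 0.842)² / (0.1854)² = 107.5, so 108 per arm.

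With 10% dropout, 108/0.9 = 120 and 108 × 1.1 = 118.8, while 107.5 × 1.1 = 118.3. The stated 118 is reproduced to within 2 women. It concerns the Mayo response; the article gives no power target for pregnancy.

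**2. Chance imbalance in age.** The article gives no age distribution. Assume ages uniform on 20 to 45:

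- SD = 25/√12 = 7.22 years.
- SE of the difference in means at 118 per arm = 7.22 × √(2/118) = 0.94; 95% range ±1.96 × 0.94 = ±1.8 years.
- At 60 per arm: 7.22 × √(2/60) = 1.32; ±2.6 years. This matters because section 3 guides only women in stable condition towards pregnancy.
- If ages cluster (SD 5, also an assumption), at 118 per arm: 1.96 × 5 × √(2/118) = ±1.3 years.

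**3. What a 1.84-year imbalance does to the estimate.** Near a 50% rate the shift is about 0.25 × |ln OR per 10 years| × 0.184:

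| OR for conception per 10 years of age | Shift, percentage points |
|---|---|
| 0.7 | 1.6 |
| 0.5 | 3.2 |
| 0.35 | 4.8 |
| 0.25 | 6.4 |

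For scale, the 95% half-width of the unadjusted difference at 118 per arm near 50% is 1.96 × √(0.5 × 0.5 × 2/118) = 12.8 points. The shift is already part of that half-width. It is not an extra error.

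**4. Power, holding the overall rates fixed.** Simulated trials compared the unadjusted chi-square test with logistic regression on arm and linear age. Assumed rates are 50% v 68%, 118 per arm, 4000 trials per row. Clustered ages are normal with mean 30 and SD 5, clipped to 20–45. Gains use unrounded values.

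| OR per 10 years | Uniform ages: unadjusted, adjusted (gain) | Clustered ages: unadjusted, adjusted (gain) |
|---|---|---|
| 1.0 | 81.0, 80.6 (−0.4) | 81.1, 80.4 (−0.7) |
| 0.7 | 80.5, 80.3 (−0.2) | 82.6, 82.2 (−0.4) |
| 0.5 | 81.7, 82.7 (+1.1) | 81.8, 81.6 (−0.2) |
| 0.35 | 80.8, 85.1 (+4.3) | 81.1, 82.0 (+1.0) |
| 0.25 | 82.2, 88.1 (+5.8) | 81.9, 84.2 (+2.4) |

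Other assumed rates (30% v 47.5%, 60% v 77%) gave +1.7 to +6.2 with uniform ages and −0.1 to +2.7 with clustered ages, for OR 0.5 and 0.25. At 65 per arm (50% v 73%) the gains were +1.0 and +5.5 with uniform ages, and 0.0 and +1.9 with clustered ages. A further run at 60 per arm ranged from about −1.5 to +5. Monte Carlo error on each power figure in the table is about √(0.8 × 0.2/4000) = 0.6 points, so differences of a few tenths mean nothing.

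**5. Power, holding the conditional odds ratio at 2.1.** 118 per arm, 6000 trials. Log-odds slopes of −0.05, −0.10 and −0.15 per year correspond to ORs per 10 years of e^−0.5 = 0.61, e^−1 = 0.37 and e^−1.5 = 0.22.

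| Slope per year | Uniform ages | Clustered ages |
|---|---|---|
| −0.05 | 77.9, 77.8 | 78.6, 78.5 |
| −0.10 | 71.5, 74.9 | 76.2, 77.2 |
| −0.15 | 60.2, 68.5 | 72.0, 74.8 |

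The fall in unadjusted power down each column partly reflects the fixed conditional odds ratio. Only comparisons within a row show the effect of adjusting. A separate run of 1500 trials with uniform ages gave 62.1 v 71.5 (9.4 points) at the steepest slope.

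**6. Type I error.** With no treatment effect, both analyses rejected in 4.1% to 5.2% of trials in every scenario.

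**The case against.** The strongest reply is that nothing is wrong with the stated test. In a randomised trial an unadjusted chi-square test is valid, and chance age imbalance is part of the sampling error that its p-value already covers. This stands. A reader might infer that the planned comparison is biased or invalid, but the documents and the calculations do not support that. The case is one of efficiency, and of an estimate that is easier to interpret if an imbalance occurs.

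Second, the size is assumed throughout. The article gives no pregnancy rate, age distribution or age effect. Its Introduction puts peak incidence in the second or third decade of life, and participants must be planning pregnancy, so clustered ages are more plausible than a flat spread to 45. This stands too. A reader might take a gain of about 9 points as the expected benefit, but that needs uniform ages and the steepest assumed slope.

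Third, these are secondary outcomes without a power target, and fewer than 118 per arm may try to conceive. This limits the importance of the point but does not remove it, because improving pregnancy outcome is among the stated aims.

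Fourth, a fuller analysis plan may add adjusted models. It may, but section 4.5 does not leave the method open: it names the test for all categorical data. Proposing a better one is a comment on a stated choice.

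Finally, nothing was computed for abnormal pregnancy. The assumed slopes concern conception, and the events may be few. That outcome should not be swept into the same model by default.

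**Conclusion.** The point holds as a free improvement of modest size, not as an error. The plan fixes an unadjusted test for pregnancy and live birth while holding, unused, a baseline variable likely to predict both. Under uniform ages the mean-age difference between arms has a 95% range of about ±1.8 years at 118 per arm. An imbalance at that limit would move the pregnancy-rate difference by about 2 to 6 points for the assumed age effects.

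The power gain from adjustment is about nil for a weak age effect. At 118 per arm it is roughly 1 to 5 points for moderate slopes with spread-out ages, or for steep slopes with clustered ages. It reaches about 6 points or more only for a strong slope with widely spread ages. With around 60 women per arm no gain can be relied on. All of these figures rest on assumed ages, rates and slopes. When age has no effect, adjusting costs less than a point of power.

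**What to change.** In section 4.5, before unblinding:

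- For pregnancy and for live birth, over all randomised women, pre-specify logistic regression on treatment and baseline age as a continuous covariate.
- Report the age-standardised risk difference with its 95% CI. It addresses the same overall difference in rates as the chi-square test, which a conditional odds ratio does not.
- Keep the chi-square or Fisher result as a supporting analysis.
- For abnormal pregnancy, use the adjusted model only if the event count supports it, under a rule set in advance; otherwise keep the stated test.

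The cost is a few sentences of analysis wording and a short extra calculation for the standardised difference. It needs no new data, visits or patients.
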